Key inclusion and exclusion criteria	Inclusion Criteria 1. Community-dwelling person 70 years of age and older receiving care from the ED, Family Medicine or Geriatric clinics at the two participating sites (MSH, NYGH) 2. Baseline de Jong loneliness score of 2.0 will be required for participating in the trial Exclusion Criteria 1. Age less than 70 years of age 2. Patients with communication problems (critically ill, unconscious, language barrier, speech impairment or otherwise unable to provide consent) or admission to a hospital for greater than 72 h) 3. Patients with severe cognitive impairment or those with living in nursing homes who are dependent on others for their activities of daily living 4. Patients without any mobile phone or landline Volunteer Inclusion Criteria 1. Peer-support volunteers will be 60 years of age or older 2. Intergenerational volunteers will be between 19–39 years of age
Study type	Interventional Allocation: Randomized interventional model. Parallel assignment. Outcome assessor masking Primary purpose: Supportive Care
Date of first enrolment	November 1, 2021
Target sample size	141
Recruitment status	Recruiting
Primary outcome(s)	1. Change in loneliness using De Jong Gierveld 6-item Loneliness Scale from baseline to 12 weeks
Key secondary outcomes	1. Change in loneliness using De Jong Gierveld 6-item Loneliness Scale from baseline to 24 weeks 2. Change in perceived social support using Lubben Social Network Scale from baseline to 12 and 24 weeks 3. Change in mood using Geriatric Depression Scale from baseline to 12 and 24 weeks 4. Change in baseline cognition using “Brief Alzheimer’s Screening Test” from baseline to 12 and 24 weeks 5. Change in Quality of Life using Euro-Qual 5 Dimensions 5 Levels from baseline to 12 and 24 weeks 6. Change in Functional Status using Older Americans Resource Scale from baseline to 12 and 24 weeks 7. Change in self-perceptions of generativity using Loyola Generativity Scale from baseline to 12 and 24 weeks 8. Perceived benefit to participant at 12 and 24 weeks 9. Perceived benefit to volunteer at 12 and 24 weeks

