### Study design and setting

We will conduct a prospective multi-centered three-arm, single-blind, superiority RCT. The study will recruit participants from three settings: (1) the ED of the Schwartz/Reisman Emergency Medicine Center, (2) the Granovsky-Gluskin Family Medical Centre at Mount Sinai Hospital, and (3) the ED of the North York General Hospital. All three sites are in Toronto, Ontario, Canada. Mount Sinai Hospital is an urban tertiary care center with an annual census of 65,000 ED patients. North York General is a university-affiliated academic community hospital with an annual census of 118,000 ED patients. For both hospitals, 17–20% of ED patients were 70 years and older over the last 3 years.

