### Hypotheses

Our primary hypothesis is that participants who receive the intergenerational HOW R U? intervention will have superior outcomes compared to the waitlist control group and to the same-generation peer support HOW R U? intervention. Our second hypothesis is that participants with higher perceptions of generativity will have greater reductions in SIL. Third, we hypothesize that participants in the intergenerational intervention will have higher perceptions of generativity after 12 weeks than the same-generation peer support and waitlist control groups.

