### Outcome measures

The primary outcome is loneliness as measured using the six-item De Jong loneliness scale after completion of the intervention (weeks 12–14 of the study). The De Jong scale has been extensively validated in older populations and is divided into four clinically relevant categories: 6—severe loneliness, 4–5—moderate-to-severe loneliness, 2–3—low loneliness, and 0–1—no loneliness [12].

The secondary outcomes are the following: (1) the de Jong loneliness Scale at 12 weeks post-completion of the intervention to assess sustainability (study week 24); (2) six-item Lubben’s Social Network Scale [18]; (3) five-item Geriatric Depression Scale to assess mood [19]; (4) Brief Alzheimer’s Screening Test to assess baseline cognitive performance [20]; (5) EQ-5D-5L to assess perceived health-related quality of life in the areas of self-care, mobility, usual activities, pain/discomfort, and anxiety/depression [21]; (6) the Older Americans Resource Scale to assess functional status [22]; (7) the Loyola Generativity Scale to assess generativity [23]; (8) perceived benefit by the participant; and (9) benefit to the volunteer as perceived by the participant. The standardized measurement instruments selected for the trial have been extensively validated in older adults. The Loyola Generativity Scale has demonstrated good interrater reliability as well as responsiveness in trials of older adults [24, 25]. To assess the secondary outcome of participant preference for same-generation peer support versus intergenerational HOW R U? intervention, we will use a 5-point Likert scale with the following options: “I strongly prefer peer support,” “I prefer peer support,” “neutral,” “I prefer intergenerational,” and “I strongly prefer intergenerational”. Please see Appendix 3 for full details.

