### Sample size and power

Each group will consist of a sample of 47 subjects which will detect a 13.9–28.1% difference between the treatment and control groups in the proportion of people who improve by one category (e.g., from severe loneliness to moderate-to-severe loneliness) with a power greater than 80%. This assumes that up to 15% of control group participants may have a spontaneous improvement in loneliness categories. With these sample sizes, three comparisons may be made: intergenerational intervention to the control group, same-generation peer support intervention to the control group, and intergenerational to the same-generation peer support intervention.

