### Analysis

All analyses will use SAS Version 9.4 (SAS Institute, Cary, NC, USA). A two-sample two-sided test of proportions will be used to assess the primary outcome of loneliness in the control group versus the intergenerational HOW R U?, and the control group versus the same-generation peer support HOW R U? intervention. Improvements in the binary outcome of the loneliness category of the De Jong Loneliness Scale will be assessed using a logistic regression model, and results will be reported as odds ratios with the corresponding 95% confidence intervals. The variance inflation factor (VIF) will be calculated to assess for multicollinearity before the logistic regression model is built such that if two variables are highly correlated (i.e., VIF > 4 or tolerance < 0.25), only one of the two variables is retained for the final model. To compare the secondary outcomes, they will be reported as means with corresponding 95% confidence intervals.

Potential missing data will be managed as follows. For logistic regression, participants with more than 15% missing data for confounding variables will be excluded from the analysis. Note that in the main trial, less than 5% of participants would have been excluded. For participants with less than 15% missing data, we will use imputation for confounding variables. Participants with missing outcome data will be excluded from analysis (i.e., lost to follow-up). Note that after two-thirds of the participants have been enrolled, we will assess the loss-to-follow-up rate and adjust the enrollment accordingly. For example, if the lost-to-follow-up rate is 20%, we will increase the enrolment by 20%. To manage protocol nonadherence, participants will be analyzed using intention-to-treat analysis regardless of their adherence to the protocol.

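### Secondary outcomes are to be compared by means with 95% intervals and no between-arm difference is named, although the third hypothesis and the secondary objectives concern differences between arms

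*Protocol article*

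**What the plan says.** The Analysis section of the protocol article gives the secondary outcomes one sentence: "To compare the secondary outcomes, they will be reported as means with corresponding 95% confidence intervals". The same paragraph treats the primary outcome differently. It has a two-sided two-sample test of proportions and a logistic model reported as odds ratios with 95% confidence intervals, both of which compare arms.

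The questions put to the secondary outcomes are also between-arm:

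- The Hypotheses section states, as the third hypothesis, that "participants in the intergenerational intervention will have higher perceptions of generativity after 12 weeks than the same-generation peer support and waitlist control groups".
- The Study purpose section lists the impact of the intergenerational intervention on depression, quality of life, function and generativity at weeks 12 and 24.
- The Study design and setting section describes a "prospective multi-centered three-arm, single-blind, superiority RCT".

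Table 2 (under Methods/design) gives the generativity endpoint as "Change in self-perceptions of generativity using Loyola Generativity Scale from baseline to 12 and 24 weeks". Table 1 marks the scales as collected before the intervention and at both follow-ups, in all groups.

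**The concern.** The third hypothesis has as its null that mean generativity is equal between arms. The quantity that bears on it is a difference of two means and the interval for that difference. The Analysis sentence promises a comparison but names a mean. An interval for one arm's mean, or for its mean change, describes that arm alone. It can show that an arm's change differs from zero, but not directly that two arms differ.

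This is more than a detail left to an analysis plan, because the article states a method, and an analysis plan that followed the sentence literally would carry the gap forward. Informal readings of separate intervals do not behave like a 5% test. Some are far too strict and others far too lenient. With no contrast fixed in advance, the choice among them stays open until the data are seen. What is at stake is the answer on generativity, the trial's proposed mechanism, and on the other secondary scales. The primary analysis and the sample size are not affected.

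**Working it through.** **The plan's own figure.** The only power statement concerns the primary outcome: "Each group will consist of a sample of 47 subjects", for a "13.9–28.1% difference between the treatment and control groups", with up to 15% spontaneous improvement among controls. At the upper end, 0.15 against 0.431 with two-sided 5% and 80% power:

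- Uncorrected: n = [1.960·√(2·0.2905·0.7095) + 0.842·√(0.15·0.85 + 0.431·0.569)]² / 0.281² = 39.8, so 40 per arm.
- With continuity correction: 47 per arm, which matches the article.

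This supplies n = 47 and nothing about the secondary scales.

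**Assumptions for the rest.** 47 analysed per arm; one pair of arms; independent arms with equal SD; effects in SD units, because the article gives no SD for any secondary scale; two-sided 5%, taken from the 95% intervals. The standard error of a difference is √(2/47) = 0.206 SD.

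**Interval for the between-arm difference.** Power = Φ(d/0.206 − 1.96).

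**Reading by non-overlap of two per-arm 95% intervals.** The means must differ by more than 1.96·(2/√47), which is 1.96·√2 = 2.77 standard errors of the difference. The false-positive rate is 2·[1 − Φ(2.77)] = 0.0056, and power = Φ(d/0.206 − 2.77).

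| True difference (SD) | Power, interval for the difference | Power, non-overlap |
|---|---|---|
| 0.3 | 30.7% | 9.4% |
| 0.5 | 67.9% | 36.4% |
| 0.578 | 80.0% | 51.2% |
| 0.8 | 97.2% | 86.6% |

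Simulation with t intervals agrees. The non-overlap rule rejected in 0.53% of 100,000 trials and 0.57% of 50,000 trials under no difference. Its power was 50.0% at 0.584 SD, where the t-test has 80%. With 38 analysed per arm (about 20% loss), power at 0.578 SD is 71.2% for the difference and 40.0% for non-overlap.

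**Reading by whether one arm's mean lies outside the other arm's interval.** The false-positive rate is 2·[1 − Φ(1.96/√2)] = 16.6%.

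**Reading by which arm's change interval excludes zero.** Let both arms have the same true change δ, in SDs of the change score. Each interval excludes zero with probability p = Φ(δ√47 − 1.96) + Φ(−δ√47 − 1.96), and the two arms disagree with probability 2p(1 − p).

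| Common change δ | p | Arms disagree |
|---|---|---|
| 0 | 0.050 | 9.5% |
| 0.2 | 0.278 | 40.2% |
| 0.286 | 0.500 | 50.0% |
| 0.41 | 0.803 | 31.7% |

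In half of these discordant trials the intergenerational arm is the one that appears to change.

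**Gain from baseline adjustment.** With baseline-to-follow-up correlation ρ, the residual variance is multiplied by 1 − ρ². At d = 0.5 SD, ρ = 0.5 gives an effective 0.5/√0.75 = 0.577 SD and ρ = 0.6 gives 0.5/√0.64 = 0.625 SD. Power from the noncentral t is about 79% and 85%, against about 67% unadjusted. The article gives no value for ρ.

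**The case against.** The strongest case on the other side has five parts.

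- **The sentence is loose, not wrong.** It does not say the means are per arm and does not exclude mean differences. It opens with the purpose of comparing, and the Sample size and power section lists three between-arm comparisons. This stands as a limit: that only arm means are intended is a literal reading, not something the article states.
- **An article condenses.** Contrasts and covariates for secondary scales are often left to the analysis plan. This stands for the model details. It does not cover a stated method which, taken at its word, does not target the stated hypothesis.
- **The difference can be recovered.** The arms are independent, so each standard error can be recovered from its interval, and √(se₁² + se₂²) gives an unadjusted interval for the difference. This is correct, and a valid between-arm answer is therefore not out of reach. It is simply not what the plan says will be reported.
- **The error rates belong to rules the plan does not adopt.** This stands. A reader might infer that power or error control has been lost for the secondary outcomes. The article does not support that, because it sets no overlap or within-arm rule and claims neither power nor multiplicity control for these outcomes.
- **Baseline may already be used.** Table 2 defines these outcomes as change from baseline, so it would be wrong to infer that baseline is ignored. Adjustment is an improvement in precision over change scores, not the repair of an error.

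**Conclusion.** The point holds in a limited form. The article says how secondary outcomes will be compared and names no between-arm difference, while the third hypothesis and the secondary objectives require one. Read literally, the reported intervals would not directly address them.

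The size is conditional on how conclusions are drawn. With 47 per arm, an overlap reading would work at about 0.5% instead of 5%, with about 50% power instead of 80% at a 0.58-SD difference. A reading by which arm's change interval excludes zero could be discordant in up to about 50% of trials in which both arms change equally. That maximum needs a common change of about 0.29 SD, which is an assumption. All the figures rest on equal SDs and independent arms, and the main ones on no loss to follow-up.

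**What to change.** Replace the Analysis sentence on secondary outcomes with:

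> For each continuous secondary scale measured at baseline, between-arm differences in mean at weeks 12 and 24 (intergenerational minus waitlist, intergenerational minus peer support, and peer support minus waitlist) will be estimated by a linear model with arm and the baseline value of that scale, and reported with 95% confidence intervals. The two week-12 Loyola Generativity Scale contrasts involving the intergenerational arm address the third hypothesis. Per-arm means are descriptive.

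The three contrasts match the comparisons listed under Sample size and power. The cost is one sentence, a standard linear model in the software already named, and a few more table rows. No new data or participants are needed, since Table 1 already collects the baseline values. The change does not adjust for multiplicity across scales, times and contrasts, so the intervals should be presented as unadjusted unless the analysis plan says otherwise.

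### Excluding everyone without a week 12–14 outcome makes the primary comparison complete-case on the outcome, not full intention-to-treat; a separate covariate rule needlessly drops participants from the logistic regression

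*Protocol article*

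**What the plan says.** All the rules stand in the second paragraph of the protocol article's Analysis section.

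- Missing outcome: "Participants with missing outcome data will be excluded from analysis (i.e., lost to follow-up". Under Outcome measures, the primary outcome is the six-item De Jong score at weeks 12–14.
- Missing covariates, many: "For logistic regression, participants with more than 15% missing data for confounding variables will be excluded from the analysis".
- Missing covariates, few: "For participants with less than 15% missing data, we will use imputation for confounding variables".
- Expected extent of the covariate exclusion: "Note that in the main trial, less than 5% of participants would have been excluded".
- Loss to follow-up: it is reviewed once two-thirds are enrolled, and enrolment is raised. The worked example is 20% loss answered by 20% more enrolment.
- Nonadherence: "participants will be analyzed using intention-to-treat analysis regardless of their adherence to the protocol".

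The first paragraph of the section assigns the primary outcome to a two-sample, two-sided test of proportions. It also plans a logistic regression of improvement in De Jong category, the same binary endpoint.

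**The concern.** A randomised comparison is protected because the groups compared are the groups randomised. Removing everyone without an outcome leaves those who stayed, and staying may depend on both arm and outcome.

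The design makes arm-related loss plausible. The trial is open-label. Participants state a preference between volunteer types and are randomised regardless, and the Discussion names preference against assignment as a potential confounder. Withdrawal is allowed at any time. Controls are offered their choice of intervention only after the 24-week assessment. No data are collected between enrolment and the end of the intervention, so a participant who leaves before then contributes nothing to the primary result.

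The covariate rule is a smaller matter. In a randomised comparison, baseline covariates add precision but are not needed for validity. A gap in them is no reason to discard an observed outcome.

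**Working it through.** **1. The plan's design figure.** Inputs from Sample size and power: 47 per group, control improvement up to 15%, upper detectable difference 28.1 points (so 43.1% in the treated group), power above 80%. Two-sided alpha of 0.05 is assumed from the two-sided test and the 95% intervals.

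n = [1.96·√(2·p̄·(1−p̄)) + 0.8416·√(p₁(1−p₁)+p₂(1−p₂))]² / d², with p̄ = 0.2905 and d = 0.281:

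[1.96·√0.4122 + 0.8416·√0.3727]² / 0.0790 = 39.8, so 40 per arm; with the continuity correction, 47. The upper end reproduces. Without the correction, power at 47 per arm is 86.3%.

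**2. What exclusion does to numbers.** The article gives no expected loss rate; 20% is only its example.

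- 47 × 0.80 = 37.6, about 38 analysed per arm. Power for 15% against 43.1% falls from 86.3% to 78.1% (no continuity correction).
- Raising enrolment by 20%: 141 × 1.20 = 169.2, so 170; 170 × 0.80 = 136 with outcomes. Keeping 141 needs 141 / 0.80 = 176.25, so 177.

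Extra recruits make good most of the number. They do not bring back the outcomes of those who left.

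**3. What exclusion could do to the estimate (all loss rates assumed).** If a fraction p truly improves, and a fraction a of improvers and b of non-improvers is lost, the rate among completers is

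p(1−a) / [p(1−a) + (1−p)(1−b)].

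If a = b in each arm there is no bias, even when the arms lose different amounts. With no true effect and p = 0.15 in both arms:

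| Active-arm loss | Control loss | Active completers | Control completers | Spurious difference | Two-sided rejection |
|---|---|---|---|---|---|
| 5% of improvers, 30% of non-improvers | 10% at random | 0.1425/(0.1425+0.595) = 19.3% | 15.0% | +4.3 points | about 8% |
| 20% of the arm, all non-improvers | 20% at random | 0.15/0.80 = 18.75% | 15.0% | +3.75 points | about 7% |
| 30% of the arm, all non-improvers | 10% at random | 0.15/0.70 = 21.4% | 15.0% | +6.4 points | about 11.5% |

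Swapping the arms in any row reverses the sign.

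**4. How much an observed result could hide.** Take 9 of 47 lost per arm and assumed completer counts of 16/38 and 6/38.

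| Treatment of the lost | Rates | Difference | p |
|---|---|---|---|
| Excluded, as planned | 16/38 v 6/38 | 26.3 points | 0.011 |
| Counted as not improved | 16/47 v 6/47 | 21.3 points | 0.015 |
| All lost controls improved, no lost treated did | 16/47 v 15/47 | 2.1 points | 0.83 |
| The reverse | 25/47 v 6/47 | 40.4 points | <0.001 |

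The last two rows are bounds, not likely values.

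**5. The covariate rule.** Its scope is the logistic regression. At under 5% of 141 it would remove at most 7 people (0.05 × 141 = 7.05). That figure concerns covariates and says nothing about lost outcomes.

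**The case against.** A reader might infer three stronger things, and the article supports none of them.

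- **That the covariate rule also makes the primary test complete-case.** It does not. The rule opens by limiting itself to logistic regression, so the unadjusted test of proportions is untouched. Covariates below the 15% threshold are imputed. What stands is that the regression analyses the same endpoint and its odds ratios will be reported, so some observed outcomes are discarded there.
- **That the paragraph flatly contradicts its intention-to-treat promise.** The sentence is framed around nonadherence. Someone who stops the calls but is assessed stays in, as allocated. What stands is that the label does not cover those lost to follow-up, so the primary result cannot be described as intention-to-treat without qualification.
- **That the exclusion will favour the active arms.** No arm-specific loss rate is given. Controls who receive nothing for 24 weeks may also disengage, which could reverse the direction. The inputs in step 3 are chosen, and even so the first case gives only +4.3 points and a rejection rate near 8%.

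Two further objections have force. Sensitivity analyses are commonly left to the analysis plan, so their absence from an article is not itself a fault; but exclusion of missing outcomes is a stated rule, not a gap. And imputation under missing-at-random would not remove the bias illustrated in step 3, because there loss depends on the unseen outcome. A large imputation model by arm would also be sparse with 47 per arm. Both objections shape the fix.

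**Conclusion.** The concern holds in a limited form. As written, the primary comparison includes only participants with a week 12–14 De Jong score, and enrolling more does not repair that. The covariate exclusion is a separate, secondary defect: unnecessary, confined to the regression, and expected to touch under 5%.

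The size and direction of bias are unknown. The assumed no-effect cases give roughly +4 to +6 points, with the sign depending on which arm loses people selectively, and none at all if loss is unrelated to outcome within each arm. With the article's 20% example, loss alone takes power at the upper design difference from 86.3% to 78.1% unless recruitment compensates.

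**What to change.** 1. State that all randomised participants are analysed as allocated, and say separately how nonadherence and missing outcomes are handled.
2. Replace the missing-outcome exclusion with multiple imputation from a small model (arm, baseline De Jong score, referral source, and the week-24 De Jong score where available), with the missing-at-random assumption written down.
3. Pre-specify a delta or tipping-point analysis and a missing-as-not-improved analysis. These carry the weight, since they probe loss that depends on the outcome. In the first row of step 3, counting the missing as not improved gives 0.15 × 0.95 = 14.25% against 0.15 × 0.90 = 13.5%, or +0.75 points in place of +4.3.
4. Delete the 15% covariate exclusion and impute missing baseline covariates for everyone. This also settles the case of exactly 15%, which neither current rule covers.
5. Report the complete-case result as a sensitivity analysis, labelled as such.
6. If enrolment is adjusted for loss, divide by one minus the loss rate.

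The cost is revised wording and modest SAS programming, with no new data items; item 6 means a few more recruits (177 against 170 at 20% loss). The downside is reliance on a stated assumption, and imputation will gain little for participants lost at both follow-ups, who have only baseline data. The change should be fixed before outcomes are seen by arm.

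### The worked rule for replacing losses raises enrolment by the loss rate itself, so at 20% loss it leaves about 45 analysable participants per arm rather than 47

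*Protocol article*

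**What the plan says.** Under Sample size and power, the protocol article states: "Each group will consist of a sample of 47 subjects which will detect a 13.9–28.1% difference", "with a power greater than 80" per cent. The control assumption is: "This assumes that up to 15% of control group participants may have a spontaneous improvement in loneliness categories". The registration table (Table 2, under Methods/design) gives "Target sample size 141", which is 3 × 47. Neither place mentions an allowance for loss to follow-up.

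Under Analysis, participants with missing outcome data are left out of the analysis. The loss rate is to be looked at once two-thirds of participants have been enrolled, and enrolment is then to be adjusted. The only description of that adjustment is an example: "if the lost-to-follow-up rate is 20%, we will increase the enrolment by 20" per cent. The planned primary test is described as follows: "A two-sample two-sided test of proportions will be used to assess the primary outcome".

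**The concern.** The adjustment is there to bring the analysed number back to the one behind the power statement. Adding the loss rate as a percentage does not do this, because the extra participants are lost at the same rate as the others. In expectation the rule returns a fraction (1 + d)(1 − d) = 1 − d² of the target, where d is the loss rate.

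What is at stake is whether the claim of more than 80% power still holds after the adjustment. If 47 per arm only just reaches 80%, even a small shortfall makes that claim untrue. If 47 carries some slack, the shortfall has no practical effect on it.

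**Working it through.** **Inputs.** From the document: 47 per arm, three equal arms, power above 80%, control improvement up to 15%, detectable difference up to 28.1 percentage points, two-sided test of proportions, participants without outcomes excluded, and the 20%-for-20% example. Two inputs are assumptions: a two-sided alpha of 0.05 (not stated, but in line with the planned 95% confidence intervals), and pairing the 28.1-point difference with the 15% control rate, giving 15% against 43.1%.

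**Step 1: reproduce 47.** With p1 = 0.15, p2 = 0.431, difference D = 0.281 and mean p = 0.2905:

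- Uncorrected: n = [1.960 × √(2 × 0.2905 × 0.7095) + 0.842 × √(0.15 × 0.85 + 0.431 × 0.569)]² / 0.281² = (1.258 + 0.514)² / 0.0790 = 39.8, so 40 per arm.
- Continuity-corrected: n/4 × [1 + √(1 + 4/(nD))]² with n = 39.8 gives 46.6, so 47 per arm.

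The corrected formula matches the stated 47 exactly, with no loss built in. So 47 is a number of analysable participants.

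**Step 2: apply the stated rule at 20% loss.**

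- On the total: 141 × 1.20 = 169.2 enrolled; 169.2 × 0.80 = 135.4 analysable, or 45.1 per arm.
- Rounded up within arms: 47 × 1.20 = 56.4, so 57 per arm (171 in total); 57 × 0.80 = 45.6 analysable per arm.
- Shortfall against 47: 47 − 45.6 = 1.4 to 47 − 45.1 = 1.9 per arm.

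**Step 3: apply the factor 1/(1 − loss).** 47/0.80 = 58.75, so 59 per arm (177 in total), with 59 × 0.80 = 47.2 analysable per arm. Before rounding this is a 25% increase.

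**Step 4: other loss rates, rounding up within arms.**

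| Loss | Stated rule, enrolled per arm | 1/(1 − loss), enrolled per arm | Analysable per arm under stated rule |
|---|---|---|---|
| 5% | 50 | 50 | 47.5 |
| 7% | 51 | 51 | 47.4 |
| 10% | 52 | 53 | 46.8 |
| 15% | 55 | 56 | 46.75 |
| 20% | 57 | 59 | 45.6 |
| 30% | 62 | 68 | 43.4 |

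The document works only the 20% case. The other rows assume that the same form applies.

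**Step 5: power for 15% against 43.1%.**

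| Method | 47 per arm | About 45 per arm |
|---|---|---|
| Continuity-corrected formula | 80.4% | 78.4% (45.1) to 78.9% (45.6) |
| Fisher's exact test | 81.9% | 79.5% (45) |
| Uncorrected z-test, formula | 86.3% | 84.9% (45.1) to 85.2% (45.6) |
| Uncorrected z-test, exact enumeration | 87.1% | 86.2% (45) |

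Under the continuity-corrected formula, the difference detectable with 80% power at a 15% control rate moves from 28.0 points to about 28.5 to 28.7 points.

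**The case against.** The strongest reply is that the effect is too small to matter. The Analysis section names a two-sample test of proportions and mentions neither a continuity correction nor Fisher's test. On the plainest reading of that test, power stays at about 85% after the stated adjustment. The sentence is also introduced as an example in a condensed article, so the full protocol may hold the exact formula. A shortfall of fewer than two participants per arm is slight beside a plan that spans control rates of up to 15% and differences from 13.9 to 28.1 points.

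Most of this stands, and it sets the severity. It does not remove the error. The example is the only definition of the adjustment in the document, and carried out as written at its own 20% it misses the target. Nothing elsewhere in the article corrects it.

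A reader might infer three stronger things that the document does not support:

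- **That the rule fails at every loss rate above zero.** That is true of the unrounded expectation, but with whole participants rounded up in each arm both factors give the same enrolment at losses up to about 7%.
- **That the trial drops below 80% power.** That depends on a continuity correction or Fisher's test. The correction is inferred from its reproducing 47; it is not stated as the planned analysis.
- **That the 20% applies only to the third of participants still to be enrolled.** This would give 94 + 57 = 151 enrolled and 151 × 0.80 / 3 = 40.3 analysable per arm. The wording refers to the enrolment without restriction and more naturally means the whole target, so no weight is put on this reading.

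**Conclusion.** The point holds as a minor arithmetic error. The stated factor (1 + loss) should be 1/(1 − loss). At 20% loss the rule leaves about 45 analysable participants per arm instead of 47. Power then falls by about 1.5 to 2 points under the formula that reproduces the sample size, which takes it from just above to just below the stated 80%. Under an uncorrected z-test it remains comfortably above.

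The shortfall itself rests only on the document's own figures. The power figures also rest on the assumed two-sided alpha of 0.05 and on pairing the 28.1-point difference with the 15% control rate. The shortfall has no bearing on bias or on the type I error rate.

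**What to change.** Replace the example under Analysis with a rule such as: final total enrolment equals 141/(1 − observed loss rate), applied to the whole target; for example, 20% loss gives 177 (59 per arm, a 25% increase). This costs one sentence and, at 20% loss, 177 − 171 = 6 to 177 − 169 = 8 more participants than the stated rule.

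Alternatively, keep the 20% increase and state that about 45 per arm are then expected to be analysable, with the power that this gives under the planned test. That needs no further participants.
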